## Methods/design

The design of this study is a naturalistic two-year follow-up of patients admitted to the trauma treatment program and the personality disorder treatment program at GGZ Friesland, the Netherlands. The study is supervised by the Department of Psychiatry, Vrije University Medical Center, Amsterdam, the Netherlands, experts in cohort studies.

### Ethical approval

The study protocol is approved by the Medical Ethics Committee of the Regionale Toetsingscommissie Patiëntgebonden Onderzoek (RTPO, registration number NL 47054.099.14).

### Participants

Patients who sought treatment at GGZ Friesland for either personality disorders or trauma-related disorders were recruited for the baseline data collection. Baseline data were collected between November 2011 and March 2014. The inclusion period of the follow-up assessment runs from February 2014 until August 2016. All patients who completed baseline assessment will be invited to participate in the follow-up study, 2 years after they completed the baseline assessment. This includes 150 patients (116 women and 34 men): 49 patients who sought treatment for traumatic experiences and were admitted to a specialized trauma-related disorders treatment program, aimed specifically at adult survivors of prolonged early childhood trauma, and 101 patients who sought treatment for personality pathology and were consecutively referred to a specialized personality disorders treatment program. For a detailed description of the inclusion at baseline, we refer to [23]. Only participants with insufficient mastery of the Dutch language were excluded. Data on non-response as well as representativeness of the baseline sample are presented elsewhere [23]. The baseline sample was considered to represent the two relevant clinical populations.

### Procedure

For follow-up, all 150 patients who participated in the baseline study will receive an information letter, which explains the background and the purpose of the study, how the collected data will be stored, guarantee of privacy and voluntary nature of the participation. The main researcher will approach patients by phone or, if they cannot be reached, by e-mail or letter; patients get the opportunity to ask questions about the study and are invited to participate. When patients agree to participate, written informed consent will be obtained and a first appointment with an interviewer scheduled. Appointments take place at a location of GGZ Friesland or, if requested, at a patient’s home. Usually it will take two or three appointments to complete the extensive assessment, depending on the patient’s preference. Patients will be asked to complete the self-report questionnaires at home. However, we offer assistance if patients have trouble filling in the questionnaires on their own, e.g. by clarifying difficult words in the questionnaires, answering questions of patients about the questionnaires or, in the case of a blind patient, reading the questions out loud. All interviewers are trained and supervised psychologists, who also conducted the assessments in the baseline collection wave. The results of follow-up assessment (present diagnosis) and the two-year course (change in symptoms between baseline and follow-up) will be communicated to the patient by the main researcher in the form of a psychological report.

### Outcome variables

Primary outcome variables are PTSD symptoms and disorder, dissociative symptoms and disorders, (symptoms of) personality disorders and symptoms of affect dysregulation. Secondary outcome variables are general psychopathology, anxiety symptoms, depressive symptoms and personality pathology.

### Predictors

To identify predictors of course outcome, demographics (gender, age) and type and duration of treatment during the follow-up period and before baseline are registered. Furthermore, dissociation and general personality features will be assessed. Also, the severity of traumatic experiences and neglect will be (re) assessed as possible predictors.

### Measurements

The assessment battery consists of five structured clinical interviews and nine self-report questionnaires. All interviews were also assessed at baseline, as well as eight out of nine questionnaires. The additional questionnaire concerns questions about received treatment outside GGZ Friesland during the follow-up period (see below).

To assess the clinical outcome variables, namely the (symptoms of) trauma-related and personality disorders respectively, in a reliable fashion, structured psychiatric interviews are used. The Clinician Administered PTSD Scale (CAPS) [25] is used to assess (symptoms of) PTSD and the Structured Interview for Disorders of Extreme Stress (SIDES) [26] to assess complex PTSD and affect dysregulation. The Structured Interview for DSM-IV Dissociative Disorders (SCID-D-R) [27] is used to assess dissociative symptoms and dissociative disorders, which includes dissociative fugue, dissociative amnesia, depersonalization disorder, dissociative identity disorder and dissociative disorder not otherwise specified. The Structured Interview for DSM Personality Disorders (SIDP-IV) [28] is used to assess (symptoms of) all DSM-IV personality disorders. All of these interviews have good to excellent psychometric properties, including test-retest reliability. At baseline, inter-rater agreement intervals for all four interviews were high (.90 to.95) [23].

The secondary clinical outcome variables include symptom questionnaires. General psychopathology will be assessed using the Symptom Checklist-90-revised (SCL-90-R) [29]. The Inventory of Depressive Symptomatology (IDS) [30] is used to assess depressive symptoms, and the Beck Anxiety Inventory (BAI) [31] to assess anxiety symptoms. Personality pathology is also measured in a dimensional way. The level of (mal) adaptive personality functioning will be assessed using the Severity Indices of Personality Problems (SIPP-118) [32], and ‘schemas’ (i.e. inner representations) using the Young Schema Questionnaire [33]. All questionnaires are well known for their good validity and reliability.

To measure the type and amount of traumatic experiences of patients in their childhood and in adult life, as a possible predictor, we use the Structured Trauma Interview (STI) [34]. This interview is specifically designed to measure negative experiences in childhood and adult life. This results in an overview of traumatic experiences as well as other adversities. Neglect, also a possible predictor, is measured by two proxy’s: the first is the Parental Bonding Instrument (PBI) [35], which examines four types of parental bonding based on two dimensions: care and overprotection (parental control). The second proxy is parental dysfunction, measured by the STI [36]. Both instruments have good validity and reliability. Dissociative symptoms, as a (possible) predictor, are measured using the Dissociative Experiences Scale (DES) [37]. General personality traits, as a possible predictor, are assessed using the Neuroticism, Extraversion and Openness Personality Inventory (NEO-PI-R) [38]. For an overview of all outcome variables, see Table 1.

**Table 1 Tab1:** Overview of all measurements

Construct	Instrument	Time period	Severity measure (interval)
PTSD	CAPS [24]	Last month	Yes
Complex PTSD	SIDES [25]	Last month	Yes
Affect dysregulation	SIDES [25]	Last month	Yes
Dissociative Disorders	SCID-D-R [26]	Last year	Yes
Personality Disorders	SIDP-IV [27]	Last year	Yes
General psychopathology	SCL-90-R [28]	Last week	Yes
Depressive symptoms	IDS [29]	Last week	Yes
Anxiety symptoms	BAI [30]	Last week	Yes
Dissociative symptoms	DES [36]	Last month	Yes
Personality pathology	SIPP-118 [31]	Last 3 months	Yes
	Young Schema Questionnaire [32]	Currently	Yes
Personality traits	NEO-PI-R [37]	Currently	No
Traumatic experiences	STI [33]	Life time	Yes
Neglect	PBI [34]	0 to 12 years	Yes
	STI [35]	0 to 16 years	Yes

Furthermore, to measure possible determinants of course outcome we collect data from the patient record system of GGZ Friesland, including score on the Global Assessment of Functioning (GAF) Scale, last reported clinical diagnosis and data on the received therapy during the follow-up period. Data on therapy will consist of doses (the amount of received therapy in minutes) and will be specified in treatment program/department (trauma-related or personality or other), group versus individual therapy, days of hospitalization and the use of medication. In case of treatment outside GGZ Friesland, patients are asked to fill in an additional form. This form contains questions on type and duration of treatment (s) received outside GGZ Friesland, number and duration of hospitalization outside GGZ Friesland and the use of medication (e.g. type, dose and duration), prescribed outside GGZ Friesland, in the two-year period after the baseline assessment. This information will be comparable to the data on therapy inside GGZ Friesland. In addition, data on treatment history before baseline is assessed with the STI [34].

### Power calculation

The sample size was settled to permit a logistic regression analysis for the dichotomous primary outcome measure “remission of PTSD after two year” being regressed on three predictors: 1) duration of treatment, 2) severity of traumatic experiences, and 3) neglect. We determined the sample size by application of the rule of having ten events per variable, which is a conservative rule [39]. We expect that that the percentage of remitted patients will be in the range of 25%–75%, implying 40 observations per predictor. Studying three predictors, the rule implies a minimal sample size of 120. A further assumption of a drop-out rate of 20%, made us aim at 150 participants at baseline.

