## Abstract

**Background:**

Trauma-related disorders and personality disorders are prevalent in survivors of chronic childhood trauma and neglect. Both conditions have serious consequences for patients, their families, society and public health and a high risk of development of chronicity. However, information on the long term course trajectories is lacking and predictors of course outcome in survivors of chronic childhood traumatization are unknown. The first aim of the current study is to identify two-year course trajectories of pathology in patients with trauma-related disorders and personality disorders. The second aim is to examine predictors of the course, including demographics, clinical characteristics and comorbidities.

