Study findings on the course of personality disorders suggest that even severe personality disorders can improve significantly within a couple of years, with the majority of the studies concerning BPD [16–19]. Two longitudinal studies, the Collaborative Longitudinal Personality Disorder Study (CLPS) [20, 21] and the McLean Study of Adult Development (MSAD) [22], focus on identifying features that influence the course of several personality disorders. Both studies conclude that a history of trauma or neglect predicts a more negative course of BPD. The CLPS also reports that patients with either schizotypical personality disorder or BPD had experienced higher rates of being physically attacked and reported more types of traumatic exposure. Furthermore, the CLPS finds that the severity of personality psychopathology, i.e. the number of criteria met, and a low score on the Global Assessment of Functioning (GAF), have a negative influence on the course of BPD after 2 years of treatment [20]. The MSAD, focusing on a longer (10-year) course of borderline personality disorder, finds that a younger age, no history of childhood sexual abuse, less severe childhood abuse and neglect, less severe violence witnessed as a child, no prior psychiatric hospitalization, absence of PTSD and anxious cluster personality disorders, as well as four facets of normal personality (low neuroticism and high extroversion, agreeableness and conscientiousness) predict an earlier time to remission of the BPD, when measured every 2 years [22].

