The primary research question is: what is the course of (symptoms of) trauma-related and personality disorders in a sample of patients in treatment over a follow-up period of 2 years? More specifically, what is the course of the core symptoms (PTSD, (symptoms of) dissociative disorders, (symptoms of) personality disorders affect dysregulation and general functioning) in a sample of treatment seeking adults with and without histories of early childhood trauma, i.e. before the age of 12? The second research question is: which variables predict course outcome after 2 year? More specifically, are demographic (gender, age) and clinical (dissociation, comorbidity in general, personality features) predictors of a (un) favourable course after 2 years? And to what extent is course outcome dependent on the type or duration of treatment (e.g., inpatient, outpatient, pharmacotherapy, psychological treatment)? The specific variables and (possible) predictors are described more extensively in the method.

Based on the theoretical model of Draijer [23, 24] and results of previous studies, we expect that type and severity of personality pathology and trauma-related pathology at baseline predict the size of improvement at follow-up, with severe (comorbid) pathology predicting less improvement than light to medium (comorbid) pathology. Furthermore, we expect that type and severity of reported trauma and neglect as well as the number of reported traumatic experiences predict the level of improvement in symptoms of trauma-related or personality disorders between baseline and follow-up. Also, we expect that level of improvement in symptoms of trauma-related or personality disorders correlates with the level of improvement of other more general psychopathology, like anxiety, depression, and general functioning. Finally, we expect that dose (amount) and type of treatment can be identified as predictors of the course of symptoms of trauma-related and personality disorders.

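### The predictor models name only remission of PTSD, so the question about predictors of unfavourable course has no matching outcome, and a net yes/no comparison can hide patients who get worse

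*Protocol article*

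**What the plan says.** The Abstract states the aim broadly: "The first aim of the current study is to identify two-year course trajectories of pathology". The research questions at the end of the Background then ask whether demographic and clinical characteristics are "predictors of a (un) favourable course after 2 years", and how far outcome depends on treatment.

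The Power calculation names one outcome for the predictor analysis, the "dichotomous primary outcome measure “remission of PTSD after two year". The planned model has three predictors: length of treatment, trauma severity and neglect. Data analysis says that logistic regression will be used to find predictors. It speaks of outcomes in the plural but points back to the Power calculation for their description.

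Data analysis also describes course in two other ways:
- PTSD diagnosis and personality disorder diagnosis (each yes/no) at follow-up are compared with baseline by chi-square, and severity scores by analysis of variance.
- The CAPS difference, follow-up minus baseline, is regressed on a changeability score or on its two components, severity of trauma and of neglect.

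Under Participants, no PTSD diagnosis is required. Language is the only exclusion, and 101 of the 150 patients came for personality pathology. Under Measurements, record data are collected as possible determinants of outcome. The therapy data include "days of hospitalization and the use of medication". Admission is not listed under Outcome variables.

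**The concern.** A question about unfavourable course needs an outcome that identifies it. Remission identifies only one kind of good course, and its complement is a mixture: among patients with PTSD at baseline, the unchanged and the clearly worse fall together. For patients without PTSD at baseline the outcome is undefined, and the article does not say whether they leave the model or how they are coded.

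The comparison of diagnostic status does not repair this if it is reported as a net change, because remissions and new cases offset each other. A mean CAPS change can offset in the same way. The signed CAPS difference does separate worse from unchanged, but it is regressed only on the trauma and neglect indexes. Gender, age, dissociation, comorbidity, personality features and treatment are not related to it.

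The study could therefore describe a cohort as stable while a sizeable part of it deteriorated, and its statements on predictors of a poor course would rest on absence of remission. The Discussion itself says that the authors do not expect only favourable courses.

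**Working it through.** **1. The plan's own figures.** Inputs from the Power calculation: three predictors; sample size set "by application of the rule of having ten events per variable"; "the percentage of remitted patients will be in the range of 25%–75%, implying 40 observations per predictor"; drop-out 20%.
- Per predictor: 10 / 0.25 = 40.
- Three predictors: 3 × 40 = 120.
- Baseline: 120 / (1 − 0.20) = 150.

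All three figures reproduce. The calculation applies the remission percentage to all 120 followed patients, which is right only if all of them had PTSD at baseline.

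**2. Who can remit.** The article gives no baseline PTSD prevalence, so it is varied here as an assumption. Patients who can remit = 120 × prevalence. Events per predictor at 25% or 75% remission = 0.25 × that number / 3. The rest can only stay free of PTSD or develop it.

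| Assumed prevalence | Can remit | Rarer class | Events per predictor | Cannot remit | New onset at 5% / 10% / 20% |
|---|---|---|---|---|---|
| 33% | 39.6 | 9.9 | 3.3 | 80.4 | 4.0 / 8.0 / 16.1 |
| 50% | 60 | 15 | 5.0 | 60 | 3 / 6 / 12 |
| 75% | 90 | 22.5 | 7.5 | 30 | 1.5 / 3 / 6 |
| 100% | 120 | 30 | 10.0 | 0 | 0 / 0 / 0 |

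At 50% remission the events double, so 60 patients would just reach 10 per predictor. In no row does new onset reach the 30 events that three predictors would need.

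**3. Offsetting changes.** Illustration with 120 followed patients, 60 with PTSD at baseline (assumed). Of these, 15 remit and 45 persist. Of the other 60, 15 develop PTSD and 45 do not.
- Prevalence at baseline: 60 / 120 = 50%. At follow-up: (45 + 15) / 120 = 50%.
- Changed status: (15 + 15) / 120 = 25%.
- Chi-square comparing the two prevalences: 0, as they are equal.
- McNemar: (15 − 15)² / (15 + 15) = 0.
- Pearson chi-square on the baseline-by-follow-up table: 120 × (45 × 45 − 15 × 15)² / 60⁴ = 120 × 1,800² / 12,960,000 = 30. This tests whether the two diagnoses are associated, not whether status changed.

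The article does not say which chi-square is meant. None of the three gives the share who worsened.

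**4. What remission would mean in the same cohort.**
- Among patients with PTSD at baseline: 15 / 60 = 25%.
- All patients, with those without baseline PTSD coded as not remitted: 15 / 120 = 12.5%, below the planning range. The other 105 mix 45 persistent, 15 new and 45 who had PTSD at neither visit.
- All patients, coded by absence of PTSD at follow-up: (15 + 45) / 120 = 50%, of whom 45 had nothing to remit from.

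The same data give 25%, 12.5% or 50%.

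**The case against.** A reader might infer that remission is the only yes/no course outcome and that the study cannot show deterioration at all. The documents do not support that. Data analysis also names PTSD and personality disorder diagnosis, each compared with baseline, and a move from no to yes is part of that comparison. The CAPS difference is signed, so worsening is a positive value. The test of the prognostic model uses this difference and not remission, so conclusions about treatability do not rest on remission alone.

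A reader might also infer that admissions are simply added to the therapy dose. Under Measurements, dose is minutes of therapy and days in hospital are a separate item. Relating inpatient care to outcome answers a stated question. The Background finding on "no prior psychiatric hospitalization" concerns history as a predictor of remission of borderline personality disorder; it does not make admission an outcome. Nothing in the article shows that records or patients' forms separate planned from crisis admissions.

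The offsetting example uses assumed, deliberately equal flows, and a table of the two diagnoses would display all four groups. Cut-offs for reliable change may reasonably be left to a fuller document. A model of new onset is probably not feasible.

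All of this stands. It does not supply an outcome for the predictor models that matches the question, and it gives remission no meaning in patients without PTSD at baseline.

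**Conclusion.** The point holds in a limited form. New onset and worsening are recorded, but no unfavourable-course outcome is defined for the predictor models. Beyond trauma and neglect, the stated predictors are related only to remission.

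The size depends on baseline PTSD prevalence, which the article does not give. At 25% or 75% remission, a correctly restricted model has 5.0 events per predictor if half the cohort had PTSD, 7.5 if three quarters did, and 10.0 only if all did. The offsetting example shows that 25% of patients can change status with no net change; it does not predict that they will. The arithmetic behind 120 and 150 is correct as far as it goes.

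The handling of hospital days is a caution about interpretation. Patients who deteriorate may be admitted because of it, so an association of hospital days with poor outcome is not evidence of a treatment effect. Making unplanned admission an outcome is a matter of preference. The word trajectories is a minor point: with one reassessment the study measures two-year change, which is how Procedure describes it.

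**What to change.** 1. Cross-classify the two CAPS diagnoses into four groups: never (absent at both visits), remitted, persistent (present at both) and new onset. Do the same for personality disorders (SIDP-IV) and dissociative disorders (SCID-D-R). Report all four counts beside any net test, and name that test. With two visits, the labels describe status at the visits and not the time between.
2. Fit the remission model only in patients with PTSD at baseline, and limit the number of predictors to what the observed events allow under the plan's own rule of ten.
3. Report the share with reliable worsening as well as reliable improvement on the CAPS, with the cut-off fixed before the follow-up data are analysed. State which of these counts as unfavourable course, and relate it to the predictors in the research questions where numbers allow. Where new-onset counts are too small to model, report them descriptively.
4. State that an association between hospital days and poor outcome will not be read as a treatment effect. If the records allow, report planned and unplanned admissions separately.

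Items 1 to 3 use data already collected and need no new patients or visits. The cost is slightly more tabulation, a smaller remission model and imprecise new-onset estimates. The separation in item 4 depends on what the records contain.

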## Discussion

As with most follow-up (longitudinal) studies, the biggest challenge of this study is to reach all patients who participated in the baseline study [23]. Response rates in follow-up studies vary from 58% to 94% [2, 3, 14, 15, 22]. While the treatment of (complex) trauma-related disorders and personality disorders tend to take a long time, chances of patients still having therapy within GGZ Friesland are rather high. This makes it easier to contact patients and lowers the risk of expired telephone numbers and old addresses. However, while at baseline assessment was part of daily clinical routine for patients referred to trauma-related disorders program, the follow-up assessment is not embedded in any particular treatment program. This could lower the response rates. We expect non-response due to patients who are not able to participate (due to i.e. emigration, physical illness or death by suicide), patients who are not willing to participate (due to i.e. lack of time or motivation) and patients which cannot be reached (due to i.e. changed telephone numbers, changed addresses). To minimalize non-response during the study period, we keep in close touch with the treatment departments and treating clinicians. Furthermore, patients get well informed, we create a pleasant atmosphere during assessment and we concern (and anticipate on) the patients’ needs, as far as possible. All risks considered, we expect a non-response rate of 20%, leaving an N of 120. This N provides enough statistical power to answer the research questions.

Using the same psychologists to conduct the assessments at baseline and follow-up has both advantages and disadvantages. Psychologists must be well trained and have clinical expertise to obtain the clinical interviews in a reliable way. Psychologists meeting those criteria are scarce. The inter-rated agreement intervals were high at baseline (.90 to.95). Using other psychologist at follow-up can lower the inter-rated agreement. On the other hand, using the same psychologist can result in a bias towards a favourable course. However, we do not expect solitary favourable courses in our hypothesis. To minimalize any form of bias, psychologists are not allowed to look-up (individual) outcome at baseline, before they conduct follow-up assessment. Furthermore, we provide personal supervision by a senior clinical psychologist and encourage to reason the scoring of clinical interviews to enhance objectivity.

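### The ten-events-per-variable sizing counts all 120 expected responders as able to remit from PTSD, so 150 secures three predictors across the stated remission range only if every patient had PTSD at baseline

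*Protocol article*

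**What the plan says.** The Power calculation section of the Protocol article names the analysis that the sample size serves: a "dichotomous primary outcome measure “remission of PTSD after two year” being regressed on three predictors", the predictors being "1) duration of treatment, 2) severity of traumatic experiences, and 3) neglect". The criterion is "application of the rule of having ten events per variable". The authors expect that "the percentage of remitted patients will be in the range of 25%–75%, implying 40 observations per predictor". They conclude: "Studying three predictors, the rule implies a minimal sample size of 120". The loss allowance follows: "A further assumption of a drop-out rate of 20%, made us aim at 150 participants at baseline".

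The Participants section describes who the 150 are: 49 patients from the trauma programme and "101 patients who sought treatment for personality pathology". Poor command of Dutch is the only reason for exclusion. The Data analysis section treats PTSD diagnosis as a yes/no variable and compares follow-up with baseline status. The Discussion repeats the figure of 120 after 20% non-response and adds: "This N provides enough statistical power to answer the research questions".

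**The concern.** A patient can remit from PTSD only if PTSD was present at the start. The sizing applies its remission range to all 120 expected responders, as if each had PTSD at baseline. Nothing in the entry rules secures that, and two thirds of the sample (101 of 150) sought help for personality pathology.

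This is the only analysis the study was sized for. If the at-risk group is smaller than 120, the stated ratio of events to predictors is not assured, and a three-predictor model could be reported as adequately supported when it is not. The sums themselves are right; the denominator is in question.

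**Working it through.** **Inputs.** From the Power calculation section: 3 predictors, 10 events per variable, 25% to 75% remitting, 20% loss. From Participants: 49 + 101 = 150 patients. The baseline PTSD share p is not given, so it is varied as an assumption. Loss is taken as 20% in patients with and without PTSD alike.

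**Reproducing the plan.** The range is symmetric and is turned into 40 observations per predictor, so the rule is being applied to the rarer outcome class (remitted or not remitted).
- Observations per predictor: 10 / 0.25 = 40
- Analysed: 3 × 40 = 120
- Baseline: 120 / (1 − 0.20) = 150
- Rarer class at the bound: 120 × 0.25 = 30, and 30 / 3 = 10.0 per variable

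All figures match, with nothing to spare.

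**Restricting to patients who can remit.**
- At risk and followed up: 0.8 × 150 × p = 120 × p
- Rarer class at remission rate r: 120 × p × min(r, 1 − r)
- At r = 25% or 75%: 30 × p, or 10 × p per variable

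| Assumed p | At risk, followed up | Rarer class at 25% or 75% | Per variable | Rarer class at 50% | Per variable |
|---|---|---|---|---|---|
| 100% | 120 | 30 | 10.0 | 60 | 20.0 |
| 80% | 96 | 24 | 8.0 | 48 | 16.0 |
| 66% (all 49 plus half of 101) | 79.6 | 19.9 | 6.6 | 39.8 | 13.3 |
| 50% | 60 | 15 | 5.0 | 30 | 10.0 |
| 33% (the 49 only) | 39.2 | 9.8 | 3.3 | 19.6 | 6.5 |

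**Share needed for 30 in the rarer class.** p = 30 / (120 × min(r, 1 − r)). This is 100% at a rarer-class rate of 25%, 83% at 30%, 71% at 35%, 62.5% at 40% and 50% at 50%.

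**Floor.** The rarer class cannot exceed half of those at risk. With fewer than 60 at-risk patients followed up (fewer than 60 / 0.8 = 75 with PTSD at baseline), no remission rate gives 30.

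**Alternative reading: 25% to 75% of all 120 responders.** At the lower bound, 30 remitters would have to come from 120 × p at-risk patients, a rate of 0.25 / p among them. At the upper bound, 90 remitters leave 120 × p − 90 non-remitters, which reaches 30 only if p = 100%. This reading does not secure the stated range either, unless patients who never had PTSD are counted as an outcome class.

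**The case against.** The strongest reply is that the size of the shortfall is unknown. The article gives no baseline PTSD rate and refers the baseline description to a separate report. A reader might infer that the model will have far too few events and will be overfitted. The document does not support that: at 50% remission, 150 meets the rule if at least half the patients had PTSD, and the Power calculation section itself calls the rule conservative. Falling below it removes the stated assurance but does not show that the model is invalid.

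The Data analysis section also leaves the number of predictors open, to be settled from the literature and the data, so three is not binding. It already plans a regression of continuous CAPS change on trauma and neglect severity, two of the three sizing predictors. Both points soften the consequence. Neither changes the statement that 120 suffices for three.

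A reader might also infer that patients without PTSD will be miscoded as remitted or not remitted. No section says that they enter the remission model, and an article may leave the analysis set to the full plan. What a fuller plan cannot do is add a step for baseline PTSD share below 100% and still arrive at 120 and 150 from these inputs.

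Nor does the point show that the whole study is too small. Predictors are the second research question. The first, the two-year course, is tested by chi-square and analysis of variance and does not use this calculation.

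**Conclusion.** The point stands in conditional form. Over the plan's own 25% to 75% range, 150 patients deliver ten events per variable for three predictors only if all of them had PTSD at baseline, and the entry rules do not provide for that. At the bounds the ratio is 10 × p. Away from the bounds the shortfall shrinks, and it disappears at 50% remission once p reaches 50%. Below 60 at-risk patients followed up, it cannot be closed at any remission rate.

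The conclusion rests on remission requiring PTSD at baseline and on the plan's 20% loss applying equally to patients with and without PTSD. The values of p are illustrations, not estimates. The Discussion's adequacy statement is not supported for the remission model.

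**What to change.** 1. Define the analysis set for the remission model as patients with PTSD on the CAPS at baseline.
2. Take that number, N_PTSD, from the baseline data, whose collection ended in March 2014.
3. Restate the expected rarer class as 0.8 × N_PTSD × 0.25, the events per variable as that figure divided by 3, and the permitted number of predictors as 0.8 × N_PTSD × 0.25 / 10 = 0.02 × N_PTSD. Three predictors need N_PTSD = 150, two need 100, one needs 50.
4. If the result is below three, reduce the predictors or use a penalised fit such as Firth's. Cite the planned continuous CAPS regression as support, noting that in all responders it addresses symptom change in a mixed sample rather than remission among cases, and that as described it does not include treatment duration.
5. Replace the adequacy sentence in the Discussion with the restated figure, given as conditional on the remission rate.

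The cost is one count from existing data and some rewording, with no further patients. The downside is that the stated figure becomes less favourable unless every patient had PTSD at baseline.
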